## Abstract

**Background:**

The HIV prevalence among student men who have sex with men (MSM) in China is substantially higher than that in the general student population. However, targeted interventions for this vulnerable population remain limited. While digital technologies and peer-led approaches have shown promise in HIV prevention among MSM, their application in university settings is underexplored.

**Objective:**

This study aims to evaluate the implementation and effectiveness of a multilevel, internet-based peer intervention model in reducing HIV and syphilis incidence, improving prevention behaviors, and increasing uptake of HIV-related services among student MSM attending university in Chengdu.

**Methods:**

This prospective before-and-after self-controlled cohort study will evaluate the effectiveness of a 12-month internet-based intervention targeting university student MSM in Chengdu. A total of 484 HIV-negative student MSM among the MSM population will be recruited through WeChat and Blued. Trained student volunteers, supervised by community-based organization staff, will deliver monthly health education, one-on-one counseling, postexposure prophylaxis navigation, and HIV or sexually transmitted infection (STI) self-testing kits via secure online platforms. Participants will complete behavioral surveys and HIV/syphilis/hepatitis C virus/hepatitis B surface antigen self-tests at baseline, 6 months, and 12 months. Primary outcomes included changes in HIV and syphilis incidence rates; secondary outcomes included changes in sexual behaviors, HIV/STI testing frequency, preexposure prophylaxis/postexposure prophylaxis uptake, and knowledge improvement.

**Results:**

As of May 1, 2025, the intervention materials and training program have been finalized, and recruitment has begun. Enrollment of participants started in April 2025. By the end of April, 127 participants had completed baseline surveys and HIV/STI self-tests.

**Conclusions:**

This study will provide empirical evidence on the feasibility and effectiveness of an internet-based peer intervention for student MSM.

## Introduction

National sentinel surveillance data showed a rapid increase in newly reported HIV cases among young students in China from 2010 to 2019. The HIV prevalence among student men who have sex with men (MSM) in China is substantially higher than that in the general student population, with regional comparisons revealing the highest prevalence in the southwest region [1].

As the economic and cultural center of southwest China [2], Chengdu was estimated to have up to 120,000 active MSM in 2018 [3]. In 2021, the estimated number of college MSM registered on social networking platforms in Chengdu reached 8401, accounting for 2.08% of the total male university student population [4]. Although students were not traditionally considered a high-risk population for HIV infection, surveillance data indicate a rapidly increasing proportion of students infected with HIV/AIDS in the 15- to 24-year age group nationwide [5]. Systematic reviews have reported HIV prevalence rates of 3.8% [6] to 4.4% [5] among university student MSM. Risky sexual behaviors are common [7]; moreover, 85% of student MSM in Chengdu reported meeting sexual partners through mobile social networking platforms [4].

To date, research on university student MSM in China has primarily relied on cross-sectional surveys [6], limiting the understanding of factors driving HIV transmission in this population. While intervention trials targeting MSM populations have been conducted, few have specifically focused on student MSM. The HIV prevalence among university student MSM highlights an urgent need for effective, evidence-based public health strategies tailored to this group [5]. Compared to other high-risk populations, prevention efforts targeting university student MSM in China remain insufficient and under-researched [8].

There is growing evidence that online interventions can effectively reduce HIV risk behaviors and promote HIV testing among MSM populations [9,10]. These findings underscore the potential of digital strategies in reducing HIV or sexually transmitted infection (STI) disparities among student MSM. Given this, it is crucial to evaluate the effectiveness of internet-based intervention programs in this population.

In this study, we aim to establish a cohort of university student MSM and implement a comprehensive intervention through social networking platforms. The intervention will include regular behavioral education, HIV testing promotion, service referrals, and postexposure prophylaxis (PEP) subsidies. Previous research has shown that young people are often influenced by their peers and surrounding environments when adopting health behaviors [11,12]. Moreover, based on Social Cognitive Theory, peer educators who share similar identities and experiences can play a vital role in promoting healthy behaviors among student MSM [13].

In recent years, government regulations on community-based organizations (CBOs) serving the MSM population have become increasingly stringent, particularly regarding their direct engagement with student populations. In Chengdu, while the local Centers for Disease Control and Prevention (CDC) and AIDS Prevention Association have recruited university student volunteers for peer education, these efforts have primarily targeted the general student population and have rarely provided comprehensive, MSM-specific interventions.

Therefore, this study proposes an innovative multilevel network peer intervention model, in which the MSM CBO staff will serve as trainers, and student MSM volunteers will act as peer educators. To our knowledge, this will be the first study in China to explore and implement such a targeted intervention model specifically designed for university student MSM.

## Methods

### Ethical Considerations

Participation in this study will be entirely voluntary, and comprehensive measures will be implemented to ensure participant anonymity and data confidentiality. The study protocol has been reviewed and approved by the Ethics Committee of the Chengdu CDC (Approval No. 2024021).

All participants were required to carefully read the electronic informed consent form prior to enrollment, which will provide detailed information about the study purpose, procedures, potential risks, and benefits. Only those who voluntarily select the “Agree” option will be permitted to proceed with the questionnaire, thereby documenting their informed consent. Participants will have the right to withdraw from the study at any time without any negative consequences.

To prevent coercion or power imbalance between peers, volunteers, and participants were matched across different universities; all volunteers must sign a confidentiality agreement; all participation is anonymous and voluntary. We also conducted dedicated confidentiality training during the pre-project orientation.

To support HIV prevention efforts, the study will provide access to evidence-based online health education, individualized counseling services, and free prevention supplies, including condoms, lubricants, and HIV/STI self-testing kits. Additionally, participants will receive modest financial compensation for completing each survey, in recognition of their time and contribution. Participants received RMB 20 (US $2.83) at baseline, RMB 20 (US $2.83) at the 6-month follow-up, and RMB 20 (US $2.83) at the final 12-month follow-up.

Potential risks primarily will involve the possible inadvertent disclosure of sensitive information related to sexual behavior. However, robust data security and privacy protection protocols will be established, including data encryption, pseudonymization of identifiers, and restricted access to sensitive information, to minimize this risk.

The anticipated benefits of participation—including increased HIV-related knowledge, improved access to prevention services, and facilitation of early detection and timely linkage to care—are expected to outweigh the minimal risks involved.

Findings from this study will be disseminated to local and national public health authorities to inform HIV prevention strategies targeting students belonging to the student MSM population. In addition, study results will be shared with the broader scientific community through peer-reviewed publications and academic conference presentations.

### Study Aims

This prospective cohort study aims to evaluate the effectiveness of a comprehensive Internet-based intervention targeting student MSM attending university. Specifically, it seeks to assess the intervention’s impact on reducing HIV-related high-risk behaviors and lowering the prevalence of HIV and other STIs within this population, using a before-and-after controlled trial design.

### Study Design

The study evolved from a 2024 local public health intervention pilot. During the ethical review in June 2024, the local ethics committee recommended that, given the sensitivity and vulnerability of university student participants, all eligible students should receive access to the intervention resources and that establishing a nonintervention control group would be ethically inappropriate. Considering this recommendation and the small, hard-to-reach population size, a randomized controlled trial was deemed infeasible. Therefore, a before-after self-controlled cohort design was adopted, allowing participants to serve as their own controls to assess within-person changes.

Guided by findings from systematic reviews indicating that a 12-month intervention period is optimal for achieving behavioral changes [14], this study will set a 12-month intervention duration, with an interim follow-up assessment at 6 months.

### Study Population

#### Inclusion Criteria

Participants will be eligible for inclusion if they meet all of the following criteria: (1) male, aged 18 years or older; (2) currently enrolled university student (including students pursuing technical diplomas or undergraduate degrees); (3) self-identified MSM, defined as having engaged in sexual behaviors with men, including mutual masturbation, oral sex, or anal intercourse; (4) confirmed HIV-negative status at baseline screening; and (5) willing and able to provide written informed consent to participate in the study.

#### Sample Size

To estimate the required sample size for a prevalent cohort under an exponential distribution assumption, we adopted the 2-sample Poisson rate comparison framework described by Shiue and Bain [15]. Detailed formulas and derivations are provided in Multimedia Appendix 1.

We assumed a baseline HIV incidence of 4 per 100 person-years (estimated from multiple MSM cohort studies in China [16-18]) and an expected postintervention incidence of 1 per 100 person-years (a 75% relative reduction), with a 2-sided α of .05, 80% power, and an anticipated 10% attrition over 12 months. Based on these assumptions, the required sample size is 484 participants.

The projected reduction to 1 per 100 person-years (75%) was empirically derived. Continuous surveillance of the MSM population in Chengdu observed a 60.9% year-over-year decline in new HIV infections between 2022‐2023 and 2023‐2024 (internal monitoring data available upon request). Building upon this trend, our multilevel intervention—integrating digital education, peer counseling, and PEP subsidies—is expected to produce further improvement. Preexposure prophylaxis (PrEP) combination-prevention intervention internationally has achieved 31.5% relative risk reduction among MSM [19], thus a 75% reduction was adopted as an empirically grounded upper-bound planning scenario.

We anticipated a 12-month retention rate of approximately 90% in this online cohort of student MSM. This assumption is informed by previous longitudinal studies among young men who have sex with men and gay/bisexual men, which have reported 12-month follow-up retention of 85% to 91% under structured follow-up procedures and supportive engagement strategies [20,21]. Given that our study uses multiple retention strategies (scheduled online follow-ups, advance notification of all incentive payments at enrollment, and close coordination through student volunteers), a 10% loss to follow-up was considered an ambitious but achievable design target. Sensitivity analyses at 25%, 50%, and 75% relative reductions and attrition rates of 10% to 20% were prespecified at the fixed N to assess feasibility and robustness (see Multimedia Appendix 2 for summary scenarios).

### Study Setting

This study is scheduled to commence in June 2025 and conclude in June 2026. The research process will consist of the following sequential phases: participant recruitment, HIV/hepatitis C virus (HCV)/hepatitis B surface antigen (HBsAg)/syphilis testing, baseline survey, intervention implementation, midterm survey, and final follow-up survey.

### Enrollment Procedure

Participant recruitment will be conducted exclusively through two internet-based channels to maximize efficiency and ensure privacy. The recruitment period is expected to last for 1 month. To ensure balanced workload distribution, each volunteer will have a preassigned recruitment quota. Once a volunteer has reached their quota, subsequent applicants will be redirected to other available volunteers. Given the estimated total sample size and the involvement of 10 student volunteers, it is calculated that each volunteer will be responsible for recruiting approximately 50 eligible student MSM participants.

#### Recruitment via WeChat

Recruitment information will be disseminated through a dedicated WeChat official account (WeChat is a Chinese multipurpose messaging, social media, and mobile payment app developed by Tencent Inc), which will publish targeted enrollment announcements clearly specifying the study’s inclusion criteria. These announcements will also provide the WeChat contact information of designated student volunteers. Interested individuals will be instructed to contact these volunteers directly via WeChat, where the volunteers will conduct eligibility screening and coordinate preenrollment HIV and STI testing.

#### Recruitment via Blued

Additional recruitment will be conducted through Blued, a popular location-based social networking application specifically designed for MSM, developed by BlueCity Holdings (Beijing, China). Student volunteers will create recruitment accounts on Blued and prioritize outreach efforts at pilot universities—institutions identified through surveillance data as having historically higher HIV prevalence rates and larger student MSM populations.

Leveraging Blued’s geolocation features, volunteers will target MSM individuals within their assigned university campuses. Given Blued’s explicitly MSM user base, recruitment through this channel is expected to contribute at least 50% of the total sample size. To ensure consistency in intervention delivery, all participants recruited through Blued will also be required to add the corresponding volunteer’s WeChat account, through which the subsequent online intervention activities will be administered.

### Incentives

Participants who complete the baseline and follow-up survey will receive a modest monetary incentive. This compensation strategy serves two primary purposes: (1) to acknowledge participants’ time and effort and (2) to foster participant retention by establishing a sense of commitment and accountability within the study.

Specifically, participants received RMB 20 (US $2.83) at baseline, RMB 20 (US $2.83) at the 6-month follow-up, and RMB 20 (US $2.83) at the final 12-month follow-up. The incentive amounts were reviewed and approved by the Ethics Committee of the Chengdu CDC (Approval No. 2024021). The total compensation has been carefully calibrated to ensure it remains modest and noncoercive while promoting continued engagement.

This incentive structure also incorporates behavioral-economics principles such as loss aversion, in which participants risk forfeiting future incentives if they withdraw prematurely. This approach encourages consistent participation without exerting undue influence.

### HIV-HCV-HBsAg-Syphilis Testing

#### Overview

Participants will be required to complete self-testing for HIV, HCV, HBsAg, and syphilis at baseline, as well as during both follow-up surveys. Only individuals who test negative for HIV at baseline will be eligible for enrollment in the cohort. All participants are tested at each follow-up using a four-in-one rapid diagnostic kit that simultaneously detects HIV, syphilis, HCV, and HBV. Any reactive screening result triggers referral for confirmatory testing in certified laboratories. If a participant tests positive for any infection marker, they are immediately referred to a certified medical institution for confirmatory diagnosis and treatment, in accordance with national guidelines.

It should be specifically noted that we have also taken into account the issue of the serological window periods. To minimize potential misclassification, we have incorporated several measures including repeat testing for recent exposures and comprehensive risk documentation.

#### Repeat Testing for Recent Exposures

Participants who report any high-risk sexual exposure within the 3 months preceding a visit are scheduled for repeat rapid testing after 2‐4 weeks.

#### Comprehensive Risk Documentation

Behavioral data from the past 3 months are collected at each follow-up survey. Participants reporting recent high-risk exposure but negative results are flagged as “possible window-period” cases and analyzed in sensitivity analyses.

Peer volunteers continuously follow up with referred participants to document their confirmatory results. The same referral and verification process applies to HIV, HCV, and HBV. This workflow ensures that all reported cases represent laboratory-confirmed new infections, minimizing classification bias.

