#### Final Confirmation and Data Entry

Only results that are confirmed by certified laboratories (eg, by treponemal and non-treponemal tests for syphilis or confirmatory assays for HIV/HBV/HCV) are entered as positive outcomes in the research database.

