### HIV-HCV-HBsAg-Syphilis Combo Rapid Testing

The study will utilize the quadruple rapid diagnostic test kit developed by Guangzhou Wondfo Biotech Co., Ltd. This assay enables the simultaneous qualitative detection of HIV-1/2 antibodies, HCV antibody, HBsAg, and Treponema pallidum antibody from whole blood, serum, or plasma samples. The test employs a lateral flow immunochromatographic assay and provides results within 15 minutes.

Each test kit includes a test cassette, desiccant pouch, dropper, and buffer vial. The HIV-HCV-HBsAg-Syphilis Combo Test is approved by the China National Medical Products Administration, ensuring its safety and efficacy for clinical application.

Independent evaluations have reported excellent diagnostic performance, with sensitivities of 99.70% for HIV, 98.71% for HCV, 98.97% for HBsAg, and 98.47% for syphilis, along with corresponding specificities of 100%, 99.33%, 99.78%, and 99.68%, respectively. This highly reliable and user-friendly assay is particularly well-suited for point-of-care testing and large-scale screening initiatives, enabling timely diagnosis and facilitating rapid linkage to appropriate health care services [22].

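### The stated case rule establishes laboratory confirmation, not newness, so infections already present at enrolment can enter the syphilis and HIV primary counts

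*Protocol article*

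**What the plan says.** Entry depends on HIV status alone. Inclusion Criteria asks for "confirmed HIV-negative status at baseline screening", and the Overview under HIV-HCV-HBsAg-Syphilis Testing repeats it: "Only individuals who test negative for HIV at baseline will be eligible for enrollment in the cohort". No criterion concerns syphilis, although all four markers are measured at entry: "Participants will be required to complete self-testing for HIV, HCV, HBsAg, and syphilis at baseline, as well as during both follow-up surveys".

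The kit is described under HIV-HCV-HBsAg-Syphilis Combo Rapid Testing: "This assay enables the simultaneous qualitative detection of HIV-1/2 antibodies, HCV antibody, HBsAg, and Treponema pallidum antibody".

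The data-entry rule is in Final Confirmation and Data Entry. "Only results that are confirmed by certified laboratories", with treponemal and non-treponemal tests as the example for syphilis, "are entered as positive outcomes in the research database". The rule attaches no condition on baseline status or on the date of infection.

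Repeat Testing for Recent Exposures schedules another rapid test 2 to 4 weeks after a visit at which a high-risk exposure in the previous 3 months is reported. Comprehensive Risk Documentation, in a paragraph that names the follow-up surveys, adds a flag: "Participants reporting recent high-risk exposure but negative results are flagged as" possible window-period cases, to be examined in sensitivity analyses. The same section then concludes: "This workflow ensures that all reported cases represent laboratory-confirmed new infections, minimizing classification bias".

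Study End Points lists HIV seroconversion, triggered by a reactive test that is laboratory-confirmed, with no date condition. It has no syphilis counterpart. Table 1 defines both primary outcomes as new confirmed cases per 100 person-years, compared with 2025 surveillance data.

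**The concern.** An incidence rate needs two things: a case that began during follow-up, and person-time from people who could become such a case. The article's only account of how newness is secured is the workflow of screening, referral and confirmation, and that workflow tests for presence.

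For syphilis, an infection present at entry and still confirmable at month 6 or 12 meets every stated condition for a positive outcome. For HIV, an infection acquired shortly before enrolment and missed by the baseline antibody test meets them too, whether it shows on the repeat test or at month 6.

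Both are primary outcomes, and so few HIV cases are expected after the intervention that one or two misclassified infections matter. The error raises the cohort's rate and so works against showing a benefit.

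**Working it through.** **1. The article's own figure.** Inputs from Sample Size: 4 and 1 per 100 person-years, two-sided α 0.05, power 80%, attrition 10%. With one person-year per participant and a two-sample Poisson comparison (normal approximation):

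n = (1.960 + 0.842)² × (0.04 + 0.01) / (0.04 − 0.01)² = 436.05; 436.05 / 0.9 = 484.5, against the stated 484.

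The planning arithmetic reproduces, so the problem lies in case classification. Person-years: 484 × 0.9 = 435.6. True HIV cases expected after the intervention: 435.6 × 0.01 = 4.4.

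**2. The rules side by side.**

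| Step | HIV | Syphilis |
|---|---|---|
| Baseline test done | yes | yes |
| Baseline negative required for entry | yes | no |
| Positive outcome entered on | laboratory confirmation | laboratory confirmation |
| Date or baseline condition on that entry | none stated | none stated |
| Rule for a positive repeat test after baseline | none stated | none stated |
| Exit from follow-up once confirmed | yes | none stated |

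Nothing stated takes the workflow from confirmed to new.

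**3. HIV.** Assumption: an undetected window of w years before enrolment (the article gives no length).

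- Carried-in cases = 435.6 × 0.04 × w.
- Infections acquired in the last w years of follow-up are missed in the same way, so the net apparent rate = 0.01 × (1 − w) + 0.04 × w.
- Apparent reduction = 1 − net rate / 0.04.
- Power = Φ[(0.04 − net rate) / √((0.04 + net rate) / 435.6) − 1.960].

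| Assumed window | Carried-in cases | Net apparent rate per 100 PY | Apparent reduction | Power |
|---|---|---|---|---|
| none | 0 | 1.00 | 75% | 80% |
| 2 weeks | 0.7 | 1.12 | 72% | 76% |
| 4 weeks | 1.3 | 1.23 | 69% | 71% |
| 8 weeks | 2.7 | 1.46 | 63% | 62% |
| 13 weeks | 4.4 | 1.75 | 56% | 50% |

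Worked line, 13 weeks (w = 0.25): 435.6 × 0.04 × 0.25 = 4.4; 0.01 × 0.75 + 0.04 × 0.25 = 0.0175; 1 − 0.0175 / 0.04 = 56%.

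Plain kit error is not the issue. At the stated 99.70% sensitivity and the cited 3.8–4.4% prevalence (π), false negatives among 484 entrants = 484 × π × 0.003 / (1 − 0.997π), which is 0.06 to 0.07 persons.

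**4. Syphilis.** The article gives neither prevalence nor incidence. Assumption: a share p is confirmed positive at baseline and all of these are confirmed again at follow-up. Carried-in cases = 435.6 × p: 4.4 at 1%, 8.7 at 2%, 21.8 at 5%, which adds 1, 2 or 5 per 100 person-years. If only a fraction is re-confirmed, these shrink in proportion.

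**The case against.** The strongest reply is that Table 1 already says new, that baseline status is measured for every marker, and that infection-specific at-risk sets are usually left to a full protocol or analysis plan, neither of which is shown. Much of that stands. No sentence says that syphilis-positive entrants contribute person-time or will be counted; a reader might infer this, but the article only fails to remove them. An analyst could remove them with data already collected. The reply does not rescue the sentence in Comprehensive Risk Documentation, however. That is a positive assertion about what the workflow ensures, and the stated rules do not support it.

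For HIV, there is an explicit baseline-negative criterion, and the repeat test can be read as covering the baseline visit. A reader might infer that HIV is as exposed as syphilis. It is not: the gap is narrower and concerns how a positive repeat test, or a month-6 positive after a pre-enrolment exposure, is classed.

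Treponemal plus non-treponemal testing may separate some past infections from active ones, but no criterion for a new infection is given.

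Two further inferences should be resisted. One is that flagged men should be dropped from the primary analysis. The flag marks men with recent high-risk exposure and negative results, in a paragraph about follow-up; removing them would take out higher-risk men and favour the intervention. The other is that the missing month-0 tick for testing in Table 2 means no baseline test. The text states baseline testing several times, so the tick is clerical.

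**Conclusion.** The assurance of newness does not follow from the stated rules, and as written they can admit baseline syphilis and window-period HIV to the primary numerators. This should be fixed before outcomes are examined; it is not fatal, because the data for the repair are already collected.

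For HIV, an assumed 4 to 13 week window carries in about 1.3 to 4.4 infections against 4.4 expected; net of end-of-study misses, the apparent reduction is about 69–56% and power about 71–50%. These figures rest on the planning rates in Sample Size and on the window length. The syphilis figure, about 4 to 22 added cases, rests wholly on an assumed 1–5% prevalence with full re-confirmation.

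A reader might go further and conclude that the bias will hide a real effect. The documents do not support that: the cohort rate is pushed upward, but the net effect on the comparison also depends on how the surveillance comparator counts cases, which is not stated.

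**What to change.** 1. Syphilis: define the primary numerator and person-time among participants negative for *T. pallidum* antibody at baseline. Report reinfection among baseline-positives separately, under a stated rule.
2. HIV: class an infection confirmed from the baseline-phase repeat test as prevalent and exclude it. Start HIV person-time at the last baseline-phase negative test.
3. Reword the sentence in Comprehensive Risk Documentation to say that laboratory confirmation establishes infection and that newness comes from a negative baseline result.
4. Keep the window-period flag as a sensitivity analysis.

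Step 2 removes only what a repeat test at 2 to 4 weeks can detect, in men who report exposure and take it. Under the 13-week assumption, 9 to 11 weeks of pre-enrolment exposure would remain: 435.6 × 0.04 × 9/52 = 3.0 to 435.6 × 0.04 × 11/52 = 3.7 infections. Under the 4-week assumption, 0 to 2 weeks remain, or 0 to 0.7 infections. That remainder is why the sensitivity analysis is still needed.

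The cost is outcome-definition wording, the loss of baseline syphilis-positives from the syphilis analysis, and a few weeks of person-time for some men. No new data are needed.
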